### Intervention Components

The workshops have been developed and piloted by a research team of psychology researchers and dietitians with clinical and teaching experience (Textbox 1). The main objectives for these workshops are intended for dietitians to be able to (1) understand the importance of behavior change, (2) define the characteristics of the COM-B model, and (3) identify opportunities to and implement behavior change techniques in practice. The first workshop will focus on developing knowledge of behavior change and the COM-B model [13]. The second workshop is focused on providing dietitians with behavior change techniques from the behavior change taxonomy [6]. These techniques were based on those shown to be effective in dietary interventions [31] and were chosen based on the most relevant techniques for practical use by dietitians. These workshops will be delivered both remotely through Teams (Microsoft Corporation) and in person. The design of these workshops is informed by behavior change techniques to target participants capability, perceived opportunity, and motivation to use behavior change techniques. These are delivered through activities and group discussions to evoke reflection, awareness of their own behavior, and problem-solving to overcome the barriers that exist across their own capability, perceived opportunity, and motivation (Multimedia Appendix 1 [6,19,32-37]).

Outline of workshops.
**Workshop 1**
Understanding behaviorExploring behavior and behavior changeIntroduction to the Capability Opportunity Motivation-Behavior ModelCase studyBehavior change techniquesWhat are behavior change techniques?Explore goal setting, problem solving, self-monitoring, and social support.Case study in small groups behavior change technique
**Workshop 2**
Behavior change techniquesFurther explore 9 additional behavior change techniques and how they might apply in practice (eg, pros and cons and reattribution).Case study in small groupsRelapse management and prevention

### Data Collection Methods

Once an expression of interest has been received through the Qualtrics survey, the participant will be asked to complete an initial baseline measure. In this baseline questionnaire, participants will be asked questions on their demographics (eg, age, gender, and highest level of qualification), current perceived knowledge and behavior (ie, use of behavior change techniques), the COM-B questionnaire [38], and preparedness as a health professional to deliver behavior change techniques. The same assessments (excluding demographics) will be repeated at the postworkshop and follow-up time points. At the postworkshop time point, the questionnaire will also include items on the acceptability of the workshops.

### Outcomes

The primary outcome of this study will be behavior change, which will be operationalized in 2 ways for dietetic practice. These outcomes include (1) a change in the number of behavior change techniques used and (2) a change in the frequency of behavior change techniques used. This change will be measured across the 3 time points. While this may not be an absolute measure of behavior change technique delivery, however, any change will capture the range of techniques taken from the workshops, which may be more indicative of the dietitians’ understanding and application of the COM-B model. To further capture the uniqueness of the behavior change techniques delivered by dietitians, the type of technique will also be measured across the 3 time points. Secondary outcomes include changes in perceived capability, opportunity, motivation, and preparedness as a health professional toward delivering behavior change techniques.

### Measures

Behavior will be measured with two items to determine (1) the use of behavior change techniques and (2) the frequency of use. The first item asks participants “Which of the following behavior change techniques do you use in practice?” Participants will indicate which of the 14 techniques they have used by rating their answer as either yes, no, or unsure. A total of 14 techniques were chosen based upon techniques used for dietary behavior change in the literature [31], as well as consultations with an advisory group of dietitians to determine the appropriateness and practicality of the techniques. A composite score will be calculated to determine the number of techniques used. A second item will also be included to identify how frequently dietitians use these techniques in practice, for example, “How often do you currently use behavior change techniques when interacting with clients?” Participants will rate this item on a 5-point Likert scale from never (0) to always (4).

Capability, opportunity, and motivation will be measured using the COM-B questionnaire [38], which has been adapted for delivering behavior change techniques when interacting with clients in health contexts. This measure includes 6 items and 6 domains that reflect each component of the COM-B model as outlined by Michie et al [13]. Participants will rate their level of agreement with each item on an 11-point scale, with items ranging from strongly disagree (0) to strongly agree (10). An example item includes “I have the PHYSICAL opportunity to deliver behavior change techniques when interacting with clients (eg, time, the necessary materials, reminders, and space).”

Perceived knowledge will be measured using 3 items related to knowledge of behavior change techniques. Each item will be rated on a 7-point slider scale. Participants will rate their level of understanding of behavior change techniques and their knowledge of 9 categories of techniques from “no understanding” (1) to “perfect understanding” (7). These categories are described in the behavior change taxonomy [39]. Scores for each statement will be summed to create a total perceived knowledge score. Item 3 will ask participants to rate their level of agreement with 3 statements relating to the use of behavior change techniques (ie, if they have used them before and if they know why they are useful). These statements are rated from “strongly disagree” (1) to “strongly agree” (7). Perceived knowledge will be assessed at the 3 time points.

The preparedness of dietitians to deliver behavior change techniques will be measured using a 6-item scale. This scale has been used with health professionals, such as pharmacists [40]. This measure is to determine if dietitians feel they are equipped to deliver these techniques as part of their consultations. Statements will be rated on a 5-point Likert scale from (1) strongly disagree to (5) strongly agree. An example includes “Dietitians need training in communication skills to enable them to deliver a behavior change techniques.”

### Process Evaluation

The process evaluation will assess dietitians’ acceptability of the 2 workshops. A total of 2 items will be included at the end of the postworkshop questionnaire, which was developed by Kothe and Mullan [41]. The first question will ask participants their level of agreeance on 14 keywords related to the facilitated workshops. For example, whether they felt the workshops were “needed, useful, appropriate, interesting, exciting, worthwhile, too short.” These will be scored on a 5-point Likert scale. The second question asks participants how satisfied they were with the workshops, rated on a 5-point Likert scale ranging from “very dissatisfied” (1) to “very satisfied” (5). At follow-up, participants will also be invited to complete a one-on-one exit interview through Microsoft Teams. These interviews will allow us to assess the experience and impact of the intervention (eg, barriers and enablers) and explore the acceptability and feasibility of the workshops. Interviews will be guided by the COM-B model [13] and are expected to take 30-45 minutes each. In addition, participants who choose to withdraw from the study will also be invited to complete 3 short open-ended questions regarding their reason for withdrawing from the study. This will provide insights into noncompleters experiences and attitudes toward the intervention.

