## Methods

### Study Design and Procedure

This study is a 2-arm randomized controlled trial with a 3-month follow-up. Participants will complete a questionnaire at baseline, immediately after the intervention, and 3 months after the intervention. Participants will express their interest to participate in the study through a Qualtrics survey. Informed consent will be obtained at the start of this survey. Following this initial survey, dietitians will be randomized in blocks of 4 into either the intervention or a waitlist control condition (1:1). Block randomization will be conducted with allocation concealment from the active research team through the use of sealed, opaque envelopes. Emails will be sent to participants with the initial baseline questionnaire, and they will be informed if they can participate in the workshops immediately or if their available workshop will be in 3 months. Once dietitians have been randomized and received their baseline questionnaire, they have been enrolled in the study as participants. Both groups will participate in both workshops and complete a questionnaire immediately after participation in the second workshop and at the 3-month follow-up. The waitlist control group will be debriefed after the final questionnaire regarding their allocation to the waitlist control group. Postworkshop data collected from the waitlist control group will also be included in the final data set. Figure 1 shows a flowchart for each group’s progression in the trial. This protocol will adhere to the CONSORT (Consolidated Standards of Reporting Trials) and SPIRIT (Standard Protocol Items: Recommendations for Interventional Trials) guidelines for randomized controlled trials [28].

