### Participants

Participants will be dietitians who are currently working in Australia and hold full membership with Dietitians Australia. Participants will be recruited using purposive sampling, through both social media advertisements and newsletters directed through nutrition and dietetic organizations, and through snowballing. Recruitment of participants will be staggered over a 12-month period. A similar intervention in behavior change for health professionals found medium to large effect sizes for changes in mechanisms of change (eg, perceived knowledge) [16]. Therefore, anticipating medium to large effect sizes, a-priori analysis was conducted in G power (Axel Buchner; *F*_1,82_=0.2; power =.80; α=.05) indicating that 42 participants in each group would be adequate [29]. This means a total sample size of 84. It is anticipated that there may be high attrition in this study. Therefore, we aim to recruit approximately 140 participants to ensure that if 50% of each group are lost to attrition, the proposed analysis will be sufficiently powered. This dropout rate of 50% is conservative given that similar interventions in training health professionals can report moderate (20%) to high (50%) attrition rates [20,30].

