### Ethical Considerations

Ethics approval was granted for this study by the Human Research Ethics Office on January 20, 2023 (HRE2023-0026). This project has also been approved by the Human Research Ethics Committee (HRE2023-0026) and the Australian and New Zealand Clinical Trials Registry (ACTRN12623000525684). Informed consent to participate in the study will be received during the initial recruitment stage before any data collection. Dietitians who are interested in participating will follow a Qualtrics survey link to the participant information sheet that details their involvement in the trial. Following this information, participants will be asked to consent to participate in the study, and if they choose to withdraw from the study, they will also consent to being contacted with follow-up questions. The workshops provided will be freely accessible and are able to be recorded as continuous professional development under Dietitians Australia.

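### The scored acceptability items are asked only after workshop 2, so dietitians who stop after workshop 1 give no rating and the scores may overstate acceptability among all who started

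*Protocol article*

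**What the plan says.** Acceptability is the third objective in the Abstract and also forms part of the first. The Conclusions make wider use of the training depend on its being acceptable as well as effective.

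Acceptability is scored in one place. Under Process Evaluation, "A total of 2 items will be included at the end of the postworkshop questionnaire". One item asks for agreement with 14 keywords on a 5-point scale; the other is overall satisfaction from 1 to 5. Study Design and Procedure fixes the timing: both groups "complete a questionnaire immediately after participation in the second workshop and at the 3-month follow-up". Data Collection Methods likewise places the acceptability items at the postworkshop time point only.

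Two further sources are planned. The first is an interview: "At follow-up, participants will also be invited to complete a one-on-one exit interview through Microsoft Teams". The second is for leavers: "participants who choose to withdraw from the study will also be invited to complete 3 short open-ended questions regarding their reason for withdrawing". The stated purpose of the second is that "This will provide insights into noncompleters experiences and attitudes toward the intervention". Ethical Considerations obtains consent for this at the outset: "if they choose to withdraw from the study, they will also consent to being contacted with follow-up questions".

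On losses, the Participants section says: "It is anticipated that there may be high attrition in this study". It cites 20% to 50% from similar training studies.

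**The concern.** Coming back for workshop 2 is partly an expression of acceptability. If ratings are collected only from people who came back, the result is conditional on something close to the quantity being measured. Someone who found workshop 1 unsuitable and did not return adds nothing to the satisfaction mean or the keyword scores. With high attrition expected, the trial could report favourable ratings while a meaningful share of starters had left unrated.

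The analysis cannot repair this later. The planned t tests of completers against dropouts cannot include acceptability, because early leavers have no score. The items are asked once, so there is no earlier rating to impute from. A rating not taken at workshop 1 is lost.

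The primary behaviour outcomes are not affected. What is at stake is the acceptability conclusion.

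**Working it through.** The protocol gives no numerical acceptability target or expected score, so there is no figure of its own to reproduce. The check has three parts.

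**1. Who can be scored.** Setting the sections side by side:

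| When the dietitian is lost | Scored items | Other planned source |
|---|---|---|
| Before any workshop (including the 3-month wait) | No, but has no workshop to rate | Withdrawal questions if they choose to withdraw |
| After workshop 1, formally withdraws | No | Withdrawal questions (text) |
| After workshop 1, silently stops | No | None at the time; an interview invitation at follow-up is not ruled out |
| After the postworkshop questionnaire | Yes | Withdrawal questions if they choose to withdraw |

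The gap is the second and third rows, and the third is the least covered.

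**2. How large the unscored share can be.** Let N be the number enrolled and L the total attrition. Let a, b and c be the numbers lost before any workshop, between workshop 1 and the postworkshop questionnaire, and after that questionnaire, so that a + b + c = L × N. The unscored share of starters is

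d = b / (N − a) ≤ (L × N − a) / (N − a) ≤ L.

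Total attrition is therefore an upper limit on d, provided that anyone who skips the postworkshop questionnaire counts as lost. With N = 140 and L from 0.20 to 0.50, at most 140 × 0.20 = 28 to 140 × 0.50 = 70 people would be unscored. The protocol does not say how losses divide among a, b and c, so d itself cannot be derived.

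**3. What that could do to the score.** The true mean among starters is (1 − d) × C + d × V, where C is the completers' mean and V is the mean that leavers would have given. The reported mean is C, so

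overstatement = d × (C − V).

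The documents give neither C nor V. Assuming C = 4.2 on the 1 to 5 scale:

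| Assumed leaver mean V | d = 0.20 | d = 0.50 |
|---|---|---|
| 4.2 | 0.20 × 0.0 = 0.00 | 0.50 × 0.0 = 0.00 |
| 3.5 | 0.20 × 0.7 = 0.14 | 0.50 × 0.7 = 0.35 |
| 2.5 | 0.20 × 1.7 = 0.34 | 0.50 × 1.7 = 0.85 |
| 1.0 | 0.20 × 3.2 = 0.64 | 0.50 × 3.2 = 1.60 |

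As percentages satisfied, assuming 90% among completers:

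- Leavers at 50%: the figure among starters is 0.90 × 0.80 + 0.50 × 0.20 = 82% at d = 0.20, and 0.90 × 0.50 + 0.50 × 0.50 = 70% at d = 0.50.
- Leavers at 70%: the same formula gives 86% and 80%.

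These are illustrations at the limiting values of d, not estimates.

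**The case against.** The strongest defence is that the authors foresaw the problem. They planned questions for people who withdraw, stated that the purpose is to learn noncompleters' attitudes, and obtained consent for the contact. In a mixed-methods process evaluation, a stated reason for leaving may tell more than a number. This stands in part: leavers' views are sought. It does not close the gap, because the answers cannot be combined with the scores and the wording does not reach those who simply stop attending.

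A second defence is that the items concern the two workshops together, so asking after both is sensible. That is fair, and it means a workshop 1 rating is a different measurement that should be labelled as such. It does not remove the need for some rating from people who saw only the first.

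A third is that the article commits to CONSORT and that denominators may be set out in a fuller plan. Reporting the number unscored would help, but it cannot supply a rating that was never taken.

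A reader might go further and infer that early leavers are ignored altogether or denied an interview. The text does not support that. The interview invitation goes to participants without restriction. Study Design and Procedure treats a dietitian as enrolled once randomized and sent the baseline questionnaire, so a person who misses workshop 2 without withdrawing may still be invited.

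**Conclusion.** The point holds as a limitation of where the scored items are placed. As planned, the acceptability scores describe workshop 2 completers, and they may overstate acceptability among all who started.

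It would be tempting to say that acceptability is overstated, by up to the amounts shown above. The documents do not support this. They contain no leaver ratings and do not say that people leave because of the training. The bias is zero if leavers would rate like completers. The 20% to 50% is total attrition, which also counts people lost before any workshop and people lost after they have been scored. The share that matters is therefore unknown and may be well below that range.

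This is a modest point about a stated objective. It is worth acting on because the missing ratings cannot be recovered afterwards and are cheap to collect.

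**What to change.** 1. Ask the satisfaction item at the end of workshop 1 and, where it fits, the keyword item, both worded for workshop 1. Later stayers and leavers then answer the same question at the same time, so any difference between them can be seen directly.
2. Add the 1 to 5 satisfaction item to the withdrawal form. Send the form also to those who miss workshop 2 without withdrawing; check that the existing consent, which is worded for people who withdraw, covers this.
3. Report acceptability for all who attended at least one workshop, alongside completers' scores and the workshop 2 completion rate. Keep workshop 1 ratings labelled separately from ratings of the full training.

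The cost is a few extra minutes per participant and one added item on an existing form. Recruitment began in June 2023, so anyone who attended before the change will have no workshop 1 rating. For them, label the scores as completers' scores and state how many starters were not scored.

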### Statistical Analysis

#### Preliminary Analyses

Missing data will be managed during the data cleaning stage using case-wise deletion for missingness greater than 40%. Considerations for the use of multiple imputations as a method for addressing missing data will be made only if appropriate. Multiple imputation as a method for handling missing data is recommended for use in randomized controlled trials [42]. Assumption testing (eg, homogeneity of variances and normality) will also be conducted. If assumptions are not satisfied, appropriate transformations will be made. Dropout analyses using independent sample *t* tests (2-tailed) will identify any significant differences between participants who complete the study and those who drop out. Per protocol, intention-to-treat analyses will also be conducted as recommended for use in randomized controlled trials to reduce sample bias [43,44].

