#### Primary and Secondary Outcomes

The primary and secondary outcome variables will be assessed at the baseline, postworkshop, and follow-up time points. A chi-square test will be used to assess if there are any differences between the intervention group and waitlist control at baseline. A 2-way repeated measures ANOVA will be conducted to compare the means between the intervention group and waitlist control group (between-subjects factor) over the 3 time points (within-subjects factor) for each of the primary and secondary variables. This analysis will be run to test for any time through conditional interactions. Demographics, such as age, gender, role of dietitian, and consultation delivery mode, will be included as covariates in the analysis. Multiple regression analyses will be used to determine whether changes (residual) in capability, opportunity, motivation, and health professional preparedness predict changes in behavior (range of use or frequency of use) at each of the 3 time points (while controlling for baseline behavior).

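### The 40% deletion rule, uncommitted imputation and a complete-case repeated-measures ANOVA are not reconciled with the promised intention-to-treat analysis at the planned attrition

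*Protocol article*

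**What the plan says.** Four statements in the protocol article bear on this point.

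- **Deletion** (Preliminary Analyses): "Missing data will be managed during the data cleaning stage using case-wise deletion for missingness greater than 40" percent.
- **Imputation** (same section): "Considerations for the use of multiple imputations as a method for addressing missing data will be made only if appropriate". No criterion for appropriateness is given, although the next sentence describes imputation as recommended for randomised trials.
- **Analysis set** (same section): "Per protocol, intention-to-treat analyses will also be conducted as recommended for use in randomized controlled trials to reduce sample bias". No population definition or missing-data method is attached.
- **Model** (Primary and Secondary Outcomes): "A 2-way repeated measures ANOVA will be conducted to compare the means between the intervention group and waitlist control group", over the three time points and for every primary and secondary variable. On timing: "The primary and secondary outcome variables will be assessed at the baseline, postworkshop, and follow-up time points".

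The Participants section sets the scale. It cites attrition of 20% to 50% in similar training studies and aims for about 140 recruits "to ensure that if 50% of each group are lost to attrition, the proposed analysis will be sufficiently powered". The dropout t tests "will identify any significant differences between participants who complete the study and those who drop out"; treatment arm is not mentioned there.

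**The concern.** An intention-to-treat analysis is meant to keep every randomised dietitian in the allocated arm. A rule that deletes people because they lack outcome data, followed by a model that needs all three values, removes the people that analysis exists to keep. The article expects heavy attrition, and participants are told at enrolment whether they attend now or in three months, so dropout could plausibly differ by arm. The comparison would then be between self-selected completers. Questionnaires that dropouts had returned would be discarded. These are choices the article itself fixes, not details it leaves to a fuller document.

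**Working it through.** **Inputs.** Three time points and the ANOVA (Primary and Secondary Outcomes); 40% threshold (Preliminary Analyses); 140 recruits, 84 required, attrition 20% to 50% (Participants).

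**Step 1: who the rule deletes.** The article does not say what the 40% is counted over, so both readings are taken.

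*Counted over a participant's three questionnaires (assumption):*

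| Pattern | Share missing | 40% rule | Standard ANOVA |
|---|---|---|---|
| Baseline only | 2/3 = 67% | deleted | not reached |
| One later questionnaire missed | 1/3 = 33% | kept | dropped unless imputed |
| All three returned | 0% | kept | analysed |

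*Counted per questionnaire:* a wholly missed wave is 100% missing and exceeds 40%, so both dropout patterns are caught.

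**Step 2: who is left without imputation.** Completers = 140 × (1 − attrition).

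- 20%: 140 × 0.8 = 112, so 28 randomised dietitians are left out.
- 50%: 140 × 0.5 = 70, or 35 per arm, so 70 are left out.

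The article's own requirement is 84. The shortfall of 70 against 84 is a separate sample-size matter, and this point does not depend on it.

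**Step 3: what optional imputation could change.** On the per-participant reading, if imputation is used after deletion, those missing one wave are restored and those with baseline only are not. At 50% attrition the analysed number then lies between 70 (all dropouts have baseline only) and 140 (all miss one wave). At 20% it lies between 112 and 140. The article does not give the split.

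**Step 4: does this imply bias in the planned test?** Assume normal outcomes, 50% retention, and selection in one arm only. Let r be the correlation of the underlying tendency to complete with the outcome at a given wave. Completers in that arm shift by r × φ(0)/0.5 = r × 0.798 SD at that wave. The planned test is of the time-by-condition interaction, so what matters is how the shift differs between waves. From baseline to follow-up that is (r at follow-up − r at baseline) × 0.798.

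- r = 0.2 at every wave: (0.2 − 0.2) × 0.798 = 0. Simulated rejection at the 5% level under no effect (between-wave correlation 0.5 assumed) stays near 5%.
- r = 0.1, 0.15, 0.2: (0.2 − 0.1) × 0.798 = 0.08 SD. Rejection is about 5.7%.
- r = 0 at baseline and 0.2 later: 0.2 × 0.798 = 0.16 SD. Rejection is roughly 10%.
- r = 0 at baseline and 0.3 later: 0.3 × 0.798 = 0.24 SD. Rejection is about 16%.

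The document gives none of these correlations. The result depends on whether dropout relates differently to baseline and to later outcomes.

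**The case against.** The strongest reply is that the article does mention multiple imputation, and that intention-to-treat analyses will be done in addition. They might therefore use a separate set to which the cleaning rule does not apply. Part of this stands: with imputation, participants missing one wave could be kept on the per-participant reading, so it is wrong to say that every analysis must be a completer analysis. It does not remove the problem. Imputation is uncommitted, deletion is placed at data cleaning and so as written precedes it, and nothing exempts the intention-to-treat set.

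A reader might also infer three stronger things that the text does not support.

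- *That the test is biased by a known amount.* Shifts of 0.16 or 0.24 SD describe a comparison at one time point under assumed one-arm selection. They carry over to the interaction only if dropout is unrelated to baseline, and with equal correlations at all waves they vanish.
- *That non-attenders supply no data.* The Study Design and Procedure section ties the postworkshop questionnaire to taking part in the second workshop. It does not say that non-attenders are denied the three-month one. Baseline is collected, and Research Data Plans provides reminders for each assessment.
- *That the dropout t tests pool the arms.* The article does not say either way.

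**Conclusion.** The point stands as an unreconciled conflict over the analysis set. Without imputation, the stated rule and model analyse 112 of 140 at 20% attrition and 70 of 140 at 50%, while the same section promises intention-to-treat. This rests on the standard complete-case form of repeated-measures ANOVA and on dropouts missing whole questionnaires. It holds under either reading of the 40%. With up to half of those randomised affected on the primary outcomes, it should be settled before analysis. It is not a demonstration of bias.

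**What to change.** 1. Remove the 40% deletion rule, at minimum for the intention-to-treat set.
2. Make the primary analysis a likelihood-based mixed model for repeated measures with time-by-arm terms, on all randomised dietitians in their allocated arm and using every returned questionnaire. Keep baseline as one of the three responses, so that a participant with baseline only still contributes.
3. Label per-protocol or completer analyses as supportive.
4. Commit to multiple imputation by arm, with a delta-adjusted version, as sensitivity analysis.
5. Include arm in the dropout analysis, for example a logistic model of dropout on arm, baseline and their interaction.
6. State that postworkshop and follow-up questionnaires are sent by date, whether or not workshops were attended.

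A narrower repair would also resolve the contradiction: exempt the intention-to-treat set from deletion and commit to imputation. The mixed model is preferred because it uses partial data directly.

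The cost is revised wording, a little more programming and some extra emails. The mixed model relies on a missing-at-random assumption, and the delta-adjusted analysis tests how far the result depends on it.

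### No analysis set is named as deciding the primary outcome, so at the planned attrition the trial could be decided on completers, or on whichever set is favourable

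*Protocol article*

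**What the plan says.** Three places in the protocol article bear on who is analysed.

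- **Preliminary Analyses** has the only sentence on analysis sets: "Per protocol, intention-to-treat analyses will also be conducted as recommended for use in randomized controlled trials to reduce sample bias". The same section prescribes "case-wise deletion for missingness greater than 40" percent and adds: "Considerations for the use of multiple imputations as a method for addressing missing data will be made only if appropriate".
- **Primary and Secondary Outcomes** gives the main analysis: "A 2-way repeated measures ANOVA will be conducted to compare the means between the intervention group and waitlist control group", over three time points, for each primary and secondary variable. It does not say which participants enter.
- **Participants** sets the recruitment target so that "if 50% of each group are lost to attrition, the proposed analysis will be sufficiently powered", and notes that similar interventions "can report moderate (20%) to high (50%) attrition rates".

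No section defines a per-protocol set, and none says which set carries the conclusion on effectiveness.

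**The concern.** The analysis-set sentence has a comma where a conjunction or an extra word is needed. It may list two analyses, per-protocol and intention-to-treat. It may instead mean that, as the protocol requires, intention-to-treat analyses will be run. On the first reading there are two sets with no order between them. On the second there is intention-to-treat plus whatever set the main ANOVA uses. On both, the deciding set is unnamed.

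This matters because the plan expects heavy loss. A set restricted to those who stay is chosen by behaviour after randomisation, so the arms need no longer be comparable. The two arms also have different routes to loss, since the waitlist group waits 3 months for its workshops. If the restricted set and the full randomised set disagree, the plan gives no rule for which result counts.

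**Working it through.** **1. How many would be left.** Inputs from Participants: "we aim to recruit approximately 140 participants", 1:1 allocation, attrition of 20% to 50%.

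- At 50%: 140 × 0.5 = 70 analysed, 35 per arm.
- At 20%: 140 × 0.8 = 112 analysed, 56 per arm.

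The article's own inflation does not reproduce. It states "This means a total sample size of 84", and 84 / (1 − 0.5) = 168, whereas 140 = 84 / (1 − 0.4). That is a separate matter on which this point does not depend.

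**2. What the stated rules do by default.** Assume missingness is counted across three questionnaires of equal weight; the article does not say.

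| Questionnaires returned | Share missing | Deletion rule (>40%) | Standard repeated measures ANOVA without imputation |
|---|---|---|---|
| Baseline only | 2/3 = 67% | deleted | excluded |
| Baseline and one later | 1/3 = 33% | kept | excluded (needs all three time points) |
| All three | 0% | kept | included |

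Unless the optional imputation is used, only dietitians with all three questionnaires are analysed. An analysis labelled intention-to-treat would shrink to the same people if run this way.

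**3. How much a free choice between two sets could inflate error.** Take two two-sided tests at .05 with no true effect and correlation r between their statistics. The chance that at least one is significant is 1 − P(|Z1| < 1.96 and |Z2| < 1.96). What matters is r.

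- *Every randomised dietitian has observed outcomes, and the smaller set is a random nested fraction p.* Then r = √p. For p = 0.5, r = 0.71 and the chance is 8.3%; for p = 0.8 it is 7.1%. This does not fit the article, where the lost half has no outcome data.
- *The lost half is multiply imputed.* Assumptions: 70 per arm, 50% lost at random, imputation from baseline and arm, change-score test, baseline–outcome correlation 0.3, 0.5 or 0.7. Simulation (4,000 trials each) gave r = 0.90, 0.92 and 0.94, and an either-significant rate of 7.7%, 6.5% and 6.1%, with simulation error about 0.4 points. A repeat with 6,000 trials each and 20 imputations gave the same r to two decimals and rates of 7.3%, 6.8% and 6.4%.
- *Intention-to-treat is run on complete cases.* The sets nearly coincide, r approaches 1 and the rate approaches 5%.

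The range that fits the article is thus about 5% to 8% for one outcome. These figures assume random loss, so they contain no selection bias. Its size cannot be computed from the document.

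**The case against.** The strongest reply is that the sentence may plan no per-protocol set at all. Intention-to-treat would then be the only set named and endorsed, and crediting it with reducing bias would be reasonable. The word *also* is weak evidence of rank, since the same section uses it for assumption testing. A condensed article may also leave the definition and ordering of sets to the full protocol or the SAP.

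Much of this stands, and it rules out some stronger readings:

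- A reader might infer that the plan sets per-protocol and intention-to-treat side by side and lets either support a claim. The text permits that but does not say it.
- A reader might infer a false-positive rate of 8.3%. That needs complete outcomes on people whom the article describes as lost, so it does not apply here.
- A reader might take the remark on motivated volunteers under Strengths and Limitations as evidence that a per-protocol set would flatter the workshops. That remark concerns small changes and limited generalisability in the whole sample; it does not compare attenders with non-attenders.

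The reply does not remove the point. The article does address analysis sets, in a sentence that supports two different plans. It also fixes data rules that lead towards completers and leaves the main ANOVA without a population. That is more than detail left for later.

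**Conclusion.** The point holds in a limited form. On either reading of the sentence, the article does not say which analysis set decides the primary outcome. Its deletion rule, optional imputation and 50% attrition allowance make a completer analysis of about 70 of 140 dietitians a likely default. The main risk is selection after randomisation, which the document gives no means to quantify.

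Inflation from choosing between sets is secondary: about 6% to 8% instead of 5% for one outcome if intention-to-treat uses imputation, and near 5% if it uses complete cases. These rates rest on random loss and assumed baseline–outcome correlations of 0.3 to 0.7. The default in step 2 rests on counting missingness across the three questionnaires.

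**What to change.** Replace the analysis-set sentence under Preliminary Analyses with wording such as:

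> The primary analysis is intention-to-treat: all randomised dietitians in their allocated arm, whatever workshops they attended, using a method that keeps those with missing follow-up (for example a mixed model on all available data, or multiple imputation). The conclusion on effectiveness rests on this analysis alone. Completer (case-wise deleted) and any per-protocol analyses are supportive only.

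Name the same set beside the ANOVA under Primary and Secondary Outcomes, and bring the deletion rule into line with it. The clause on missing follow-up is essential: under a complete-case repeated measures ANOVA, the intention-to-treat label would change little. If a per-protocol analysis is intended, define its set and do not credit it with reducing sample bias.

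The cost is a few sentences and, if a mixed model is chosen, a different model for the main comparison. Recruitment and data collection are unchanged. The downside is that a result positive only among completers or per protocol could not be claimed.
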